### Measurements

In-person evaluations occur before randomisation, at intervention period midpoint (12 weeks±1 week; no MRI study at this time point), and at intervention period end (24 weeks±2 weeks) (figure 1, table 1).

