### Sample size

In the DIRECT trial, remission was 46% at 1 year (vs 4% in control arm; OR 19.7).^9^ Even higher remission was observed over the shorter term in other studies.^57^ We initially allowed for a minimum 45% remission at 24 weeks in the intervention group and up to a 5% remission rate in the control group. Using a Fisher’s exact test with 90% power, a significance of 0.05, and a 1:1 ratio between intervention and control groups, we estimated needing 56 individuals to complete the trial (control=28, intervention n=28). Allowing for up to 30% drop-out, we planned to recruit 80 individuals in total (40 UK, 40 Canada) in our successful application for funding to the MRC and the Canadian Institutes of Health Research.

We subsequently obtained additional funding from the Canadian JR McConnell Foundation, and increased recruitment goals in Canada from 40 to 60 participants (40 UK, 60 Canada). With an overall sample size of 100 (40 UK, 60 Canada), if 70 (70%) complete the trial, we will have 90% power to detect a minimum 35% remission at 24 weeks in the intervention group and up to a 5% remission rate in the control group.

Retention of at least 35 participants in each arm (70 total) will provide over 80% power to detect a difference in mean peak early diastolic strain rate of 0.10/s difference, equivalent to the exercise effect in the DIASTOLIC trial (see BACKGROUND),^18^ assuming that the common SD is 0.144 as in the DIASTOLIC trial and using a two group t-test with a 5% two-sided significance level.

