### Statistical analyses

Our primary outcome measures the proportion of remission in the intervention arm relative to the control arm. We will apply intention-to-treat principles for the primary outcome, assuming that remission of diabetes did not occur if information is not available. Based on the DiRECT and DIADEM-I trials, we estimate that remission counts in the control arm could be less than 2. We will therefore use stratified Fisher’s exact test statistics (ie, stratification by country and by sex) if remission counts are low in the control arm but consider Pearson χ^2^ test, if appropriate. If numbers permit, logistic ORs with 95% CIs (exact method) will also be performed to further quantify the efficacy of intervention over the control group, after adjusting for factors used to stratify the randomisation (country, age or sex); we will not have missing values for these covariates. Subgroup analyses for the primary outcome will be performed by country, sex and the degree of weight loss (<5%, 5%–10%, 10%–15%, >15% as examined in the DiRECT trial,^9^ collapsing categories as needed, and by exercise adherence (<50%, >50% of supervised sessions attended). In a per-protocol analysis, we will restrict the intervention group to those who achieved at least 10% wt loss and adhered to at least two thirds of prescribed exercise sessions.

We will analyse dichotomous secondary outcomes (eg, diabetes remission at 12 weeks, hypertension remission at 12 and 24 weeks) as described for the primary outcome. We will analyse continuous key secondary outcomes (eg, left ventricular peak early diastolic strain rate, lean soft tissue mass) through linear regression or log-linear regression, as appropriate, with stratification by country and sex.

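### The stated model for continuous key secondary outcomes, including peak early diastolic strain rate, names country and sex but no baseline value, and leaves the response undefined

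*Protocol article*

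**What the plan says.** Under Statistical analyses, PEDSR and lean soft tissue mass are the two examples given of continuous key secondary outcomes. The article describes the model for this group in one phrase: "through linear regression or log-linear regression, as appropriate, with stratification by country and sex". Country and sex are the only terms named. The response variable is not defined.

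Under Sample size, PEDSR has its own power statement: "Retention of at least 35 participants in each arm (70 total) will provide over 80% power". The target is a between-arm difference of 0.10/s, and the power is computed "using a two group t-test with a 5% two-sided significance level". The planning SD is given as follows: "assuming that the common SD is 0.144 as in the DIASTOLIC trial". The 35 per arm matches the retention assumed for the trial of 100 participants: "if 70 (70%) complete the trial". The text does not say whether 0.144 is the SD of a single measurement or of a change.

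Under Measurements, "In-person evaluations occur before randomisation"; two further assessments follow, one halfway through and one when the intervention ends. MRI is left out only at the midpoint, so a pre-randomisation MRI is implied. The Aims section describes PEDSR as highly reproducible on repeat measurement. The Discussion speaks of ascertaining changes in diastolic function and lean mass.

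**The concern.** The abstract names PEDSR as a key secondary outcome, and it is the only secondary outcome with a power calculation. A participant's own baseline is usually the strongest predictor of a continuous follow-up value. The stated adjustment set leaves it out, while keeping two factors that may explain much less.

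Two things are at stake. One is precision: power just above 80% at 35 per arm is exposed to slightly worse retention or a slightly larger SD. The other is that the text fits three estimators: the week-24 value without baseline, the change from baseline, and the week-24 value adjusted for baseline. These differ in power, and in how a chance baseline difference between arms enters the estimate.

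**Working it through.** **Inputs from Sample size:** n = 35 per arm, difference 0.10/s, SD 0.144, two-sided 5%, two-group t-test. **Assumed, because the article gives no figure:** correlation r between baseline and week-24 PEDSR, 0.3 to 0.8, taken within arm, with equal variances at the two times.

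**1. The plan's own figure.** Standard error = 0.144 × √(2/35) = 0.0344. Noncentrality = 0.10 / 0.0344 = 2.905. The noncentral t with 68 df gives 81.7% (82.8% by normal approximation). The stated figure of over 80% is right. On margin: 34 per arm gives 80.5% and 33 per arm gives 79.3%.

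**2. If 0.144 is the SD of the week-24 value.** ANCOVA residual SD = 0.144 × √(1 − r²). For r = 0.5 this is 0.144 × 0.866 = 0.1247. The SD of a change score is 0.144 × √(2(1 − r)). ANCOVA power uses 67 df.

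| r | ANCOVA residual SD | Week-24 value, no baseline | Change score | ANCOVA |
|---|---|---|---|---|
| 0.3 | 0.1374 | 81.7% | 67.7% | 85.1% |
| 0.5 | 0.1247 | 81.7% | 81.7% | 91.1% |
| 0.7 | 0.1028 | 81.7% | 95.9% | 98.0% |
| 0.8 | 0.0864 | 81.7% | 99.5% | 99.8% |

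**3. If 0.144 is the SD of change.** The single-measurement SD is then 0.144 / √(2(1 − r)). Multiplying by √(1 − r²) gives an ANCOVA residual SD of 0.144 × √((1 + r)/2).

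| r | ANCOVA residual SD | Week-24 value, no baseline | Change score | ANCOVA |
|---|---|---|---|---|
| 0.3 | 0.1161 | 92.3% | 81.7% | 94.4% |
| 0.5 | 0.1247 | 81.7% | 81.7% | 91.1% |
| 0.7 | 0.1328 | 60.2% | 81.7% | 87.4% |
| 0.8 | 0.1366 | 44.1% | 81.7% | 85.5% |

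**4. Cost if baseline predicts nothing.** With r = 0 and one df spent, power is still 81.7%.

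**5. Reading the tables.** ANCOVA has the highest power in every row. The two simpler analyses change places at r = 0.5. Which of them is worse, and by how much, depends on r and on the meaning of 0.144, neither of which the article gives.

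**6. Chance imbalance.** If the baseline SD is also 0.144, the difference in baseline means between arms has a standard error of 0.0344/s, about a third of the 0.10/s target. An analysis without baseline carries r times any such difference into the estimate: at r = 0.5, a one-standard-error imbalance moves it by 0.5 × 0.0344 = 0.017/s.

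These figures leave out the small effects of the country and sex terms. If those terms explain part of the same variance, the relevant r is the correlation within strata.

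**The case against.** The strongest reply is that silence is not exclusion. This is a condensed article, a statistical analysis plan may exist, and a full covariate list for secondary outcomes often sits there. The Discussion's reference to changes suggests that baseline may already be used. Planning on an unadjusted t-test is ordinary and conservative, and does not commit the analysis to being unadjusted. All of this stands. A reader might infer that the trial will discard the baseline, or that its power figure is wrong; the article supports neither. What survives is that the article does state a model, names PEDSR as an example under it, and lists terms that omit baseline.

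Other stronger inferences also lack support:

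- **Every participant will have a baseline PEDSR.** Baseline MRI is implied, but complete data are promised only for the covariates used to stratify randomisation.
- **High reproducibility implies r of 0.5 or more.** Repeatability of a measurement is not a 24-week correlation with an intervention in between, so the range has to start lower.
- **The week-24 effect will be below 0.10/s because supervision has been tapered.** No attenuated figure is given. The maintenance phase keeps an exercise target and brings back supervised sessions, and this intervention adds diet and resistance training.
- **Site should replace country.** Randomisation is stratified by country and sex, the model follows that design, and nothing in the article quantifies a gain from site.
- **A repeated-measures model would recover information.** It may for outcomes measured at weeks 12 and 24, but not for PEDSR, which has no week-12 MRI.

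**Conclusion.** The point holds as an inexpensive improvement and a needed clarification. The stated model omits the baseline value and leaves the response open, while PEDSR power is 81.7% with little room to spare. Baseline adjustment raises it to between 85.1% and 99.8% if 0.144 is the week-24 SD, or to between 94.4% and 85.5% if it is the SD of change, as r goes from 0.3 to 0.8. The unknown meaning of 0.144 alters the size of the gain but not its direction. The size rests on an assumed correlation, equal variances at the two times, and the protocol's own effect, SD and retention. The direction needs only a correlation that is not negligible.

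**What to change.** State in the analysis section that the follow-up value of each continuous outcome is analysed by ANCOVA on arm, the baseline value of that outcome, country and sex, with the baseline on the same scale as the response where a log model is used. State in the sample-size section whether 0.144 is the SD of the week-24 value or of change. If the analysis plan already contains the baseline term, a sentence saying so is enough.

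The cost is wording and one degree of freedom per model. No new visit, measurement or participant is needed, and the sample size need not change. Adjusting for site in place of country, or using a repeated-measures model for outcomes measured at both weeks 12 and 24, is optional and separate from this point.

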### Process evaluation analyses

At least two trained team members will independently code transcripts for themes,^58^ continually refining existing codes and identifying new ones. We will use Dedoose V.7.0.23 and NVivo analysis software to facilitate data coding/organisation.

### Data management

Data management is facilitated by institutional REDCap systems, with access controlled through Active Directory Technology. Data and images shared across participating centres use secure data transfer systems with all identifiable information removed. Within REDCap, we have derived plausible ranges for all outcome measures; values outside these ranges are automatically flagged and verified for accuracy.

## Discussion

Low energy diets incorporating meal replacements can achieve T2DM remission through weight loss,^9–11^ but may reduce lean mass.^18 19^ Exercise can preserve lean mass^18 19^ and directly lower insulin resistance.^13 20 50 59 60^ Combined aerobic and resistance training yields additive glucose-lowering benefits.^20^ Regular exercise reduces CVD events^61–64^ and improves MRI-based measures of heart health.^18^ RESET for REMISSION will quantify remission of T2DM in young adults achieved through a combined low energy diet and supervised aerobic and resistance training intervention and will also ascertain changes in diastolic function, lean mass and other factors that may impact long term outcomes.

Since funding was awarded for RESET for REMISSION, the literature has continued to evolve, with publication of the DIADEM-I trial, which targeted remission in younger adults less than 50 years of age of West Asian or North African ancestry. DIADEM-I combined a low energy diet (800–820 kcal/day) with exercise prescription from a trained professional centred on walking activities and self-monitoring tools, with resistance exercises introduced as the intervention progressed. While this trial did not include supervised exercise training, the objective measurement of physical activity, or cardiac function and structure, it does provide robust evidence that a low energy diet combined with physical activity can be combined in younger adults with T2DM while leading to an equivalent level of remission as has been shown in older populations, such as DiRECT.

While young persons with T2DM stand to gain the most from remission,^24^ their daily life demands may render recruitment and adherence challenging. We have endeavoured to mitigate this by integrating virtual communication tools for monitoring and follow-up where possible. Recruitment itself may be challenging in these younger individuals, as they remain fewer in number than middle-aged and older individuals with T2DM.^27^ We are, therefore, collaborating with a wide network of practices and drawing on other diabetes research cohorts in which participants have provided permission to be contacted for trials.

The international diabetes remission panel underscored the importance of evaluating the impacts of non-glycaemic measures during remission.^3–6^ RESET evaluates not only lipid profiles and MRI measures of pancreatic, hepatic and visceral fat but also sensitive MRI-based indicators of heart health for a comprehensive picture of intervention impacts. Equally importantly, we seek to understand impacts on quality of life, diabetes distress and mood.

The Canada-UK collaboration that underpins our trial will allow a wider sharing of knowledge and perspectives than in a single-country study, challenging all to learn from best practices in each jurisdiction. The DiRECT trial led to an ongoing 5000 person pilot by the National Health Service in the UK for prescribing meal replacements as part of routine T2DM management.^53^ The visibility of the current trial and the Canada-UK partnership could be an important step towards considering implementing such an intervention with integration of exercise in Canadian healthcare jurisdictions. Indeed, a future trial may seek partners beyond these two countries, to move from a demonstration of efficacy to one of effectiveness across a wide range of settings, and a plan for implementation. This is a critical journey not only to meet the glycaemic definitions of diabetes remission but also to establish its potential myocardial and vascular effects.

### Trial steering committee

This committee is responsible for the overall oversight of the trial and will review and approve protocol amendments, any substudy proposals, and will review recruitment rates, protocol adherence, retention, compliance, safety issues, planned analyses and reports, and will act on recommendations of the data monitoring committee. The trial steering committee includes an independent chair ([name], University of Glasgow), an independent clinician ([name], University of Toronto), the Nominated Principal Investigators ([name], McGill University and [name], University of Leicester), the key site investigator in Edmonton ([name], University of Alberta) and the trial statistician ([name], McGill University). The trial steering committee’s operations are described in its charter (online supplemental appendix 2).

10.1136/bmjopen-2022-063888.supp2Supplementary data

### Data monitoring committee

The data monitoring committee is responsible for the interests and safety of the participants and its main role will be to make advisory recommendations to the trial steering committee. It includes an independent clinician ([name], Nuffield Department of Primary Care Health Sciences, University of Oxford), an independent chair ([name], University of Montreal) and independent statistician ([name], University of Cambridge). The data monitoring committee is independent from the sponsors and operates in conformity with a charter (online supplemental appendix 3).

10.1136/bmjopen-2022-063888.supp3Supplementary data

### Patient and public involvement

This group will provide feedback throughout the trial on recruitment, evaluation, and retention strategies and alternatives. They will be involved in interpretation of findings and knowledge dissemination efforts, including manuscript coauthorship, presentations and interviews. The partners in Canada include [name], [name] and [name], who is Executive Director of Diabetes Quebec. [name] is a patient partner trainer who assisted with training of the patient partners. [name] is a patient partner based in the UK.

## Dissemination

We will publish the results of this trial in peer-reviewed journals and disseminate further in the scientific community through educational and conference presentations and social media targeting health professionals and the scientific community. We will share findings with the general public through press releases, media interviews and social media forums. The trial patient partners and participants will be invited to assist with knowledge sharing, including media interviews and op-eds.
